### Cost-effectiveness analyses

3.3

#### Cost-analysis

3.3.1

The TiC-P Midi will be utilized to quantify costs associated with patient care and productivity losses. The TiC-P will be adapted for this study to accurately reflect healthcare consumption in the target population and the treatment received. The units of healthcare consumption (e.g., contacts, sessions, hospital days) will be multiplied by their full economic cost-price as published in the appendix of the Dutch guideline for costing in healthcare (Zorginstituut Nederland, 2016 or later when an update becomes available). Medication costs will be calculated based on the Daily Defined Dosage (www.medicijnkosten.nl). All costs will be indexed to the reference year 2018. Cumulative costs over 9- and 18-month follow-up periods will be calculated using the area under the curve method. Costs (and effects) will be discounted as appropriate when exceeding the time horizon of 12 months and the discount rates will be subject to sensitivity analysis.

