**Methods:**

Patients aged 18 or older with SMI-PD receiving care at GGZ Rivierduinen and GGZ Altrecht (*n* = 160), mental health facilities in the Netherlands, will be recruited for this controlled naturalistic longitudinal cohort study. To assess treatment effectiveness and cost-effectiveness, self-report questionnaires will be administered and an electronic diary through the Experience Sampling Method will be used at three time points: at baseline (T0; start of treatment), and after 9 (T1) and 18 (T2) months of treatment. The questionnaires and diary will assess demographics, personality, social, and societal functioning, mentalizing capacity, epistemic mistrust, childhood trauma, attachment security, suicidality, and psychological resilience. A qualitative interview will be held at the end of treatment to evaluate treatment experiences. Additionally, therapists will complete questionnaires to evaluate the effectiveness of AMBIT. Data will be analysed using intention-to-treat multilevel regression analysis.

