### Design

2.1

This controlled, naturalistic, longitudinal cohort study will follow participants over 18 months of treatment to assess recovery outcomes in patients with SMI-PD across three settings: FACT, AMBIT-PD, and AMBIT informed-MBT. A naturalistic design was chosen to enhance ecological validity and generalizability, allowing treatment to reflect real-world practice rather than rigid protocols. Unlike a randomized controlled trial (RCT), which prioritizes internal validity, this approach better captures treatment effectiveness in complex, real-life settings where patient motivation—key to therapeutic success— will not be affected by randomization (40–43). Since participants must have already been in mental health care for at least two years (6–8), altering their current care for the sake of an RCT may be unethical and disruptive. The flexibility of the AMBIT approach, which focuses on restoring trust and adapting to individual needs, would also be compromised by a rigid study design, potentially increasing epistemic mistrust and disengagement (42). A naturalistic design minimizes exclusion due to strict criteria and reduces drop-out, leading to more complete data. However, the absence of randomization does increase the risk of bias from unknown confounders, which will be considered in the analysis (40, 42–44).

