##### Cost-effectiveness

2.3.2.8

Health-related quality of life will be assessed using the Dutch version of the EQ-5D-5L (66). The EQ-5D-5L is a self-report measure that evaluates health across five dimensions: mobility, self-care, usual activities, pain/discomfort, and anxiety/depression. Each dimension is rated on a 5-point scale ranging from 1 (*no problems*) to 5 (*extreme problems/unable to*), generating a health state that can be converted into a utility score (67). The Dutch tariff (68), will be used to derive utility values from EQ-5D-5L responses, from which quality-of-life adjusted life years (QALYs) will be calculated over the 3 years follow-up period. One QALY represents a year lived in a state of perfect health, combining both quality and length of life into a single metric. Symptom reduction and improvements in daily functioning are expected to increase QALYs, resulting in a dominant incremental cost-utility ratio (greater QALY health gains for lower healthcare costs and non-healthcare costs). These findings would support AMBIT as a more cost-effective treatment compared with treatment as usual (i.e., FACT) (69).

Individual capability will be assessed using the Dutch version of the ICECAP-A (70–72). The ICECAP-A measures five capabilities relevant to quality of life: stability, attachment, autonomy, achievement, and enjoyment. Each of five items is rated on a 4-point Likert scale ranging from 1 (not able to experience capability at all) to 4 (fully able to experience capability). Responses will be transformed into a capability index score using a tariff based on the Dutch general population. Index scores range from 0 (no capability) to 1 (full capability). The ICECAP-A demonstrates good test-retest reliability (ICC = 0.79) and construct validity in a large Dutch population (72), and has acceptable levels of content validity (70, 73).

Healthcare costs will be measured using the Treatment Inventory of Costs in Patients with psychiatric disorders (TiC-P) Midi (74), a self-report instrument consisting of 8 items. The TiC-P will be administered at each assessment and captures costs related to both intervention costs and use of health care services. These costs cover outpatient services, including therapy costs for both treatment as usual (TAU, i.e., FACT) and AMBIT programs, medical specialist and paramedic visits, home care assistance, and medication.

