### Study procedures

2.4

After recruitment, names of interested individuals will be communicated to the researchers of the study, who will then invite each potential participant for a meeting during which screening will take place and information on the study will be provided. When a potential participant is eligible and agrees to participate in the study, an informed consent must be signed. Eligible participants who have given informed consent will receive an email containing a notification of eligibility, explanation of the study, and an invitation for the baseline assessment (T0).

The baseline assessment will be held at the department where treatment takes place, which will also minimize the risk of dropout due to missed assessment appointments.

Follow-up assessment will take place during treatment, at 9 months (T1) and 18 months (T2). After 18 months, participants will continue their treatment if this is still needed, but study participation will end. Participants will be asked if they are willing to participate in assessment 5 years after the study is completed. **Table 1** presents the measurements used in each stage of the study.

**Table 1 T1:** Overview of assessments and their content.

Instrument	Time to complete	T0 Baseline	T1 After 9 months of treatment	T2 After 18 months of treatment, end of study participation
Instruments administered to the participant				
OQ-45.2	5 minutes	X	X	X
SIPP-SF	15–20 minutes	X	X	X
RFQ	3 minutes	X	X	X
QET	5 minutes	X	X	x
CTQ	5 minutes	X	–	–
YCAS	2 minutes	X	–	–
C-SSRS	2 minutes	X	X	X
ACS-30	15 minutes	X	X	X
ESM	2 minutes 10 times a day, for 5 consecutive days	X	X	X
EQ-5D-5L	5 minutes	X	X	X
ICECAP-A	5 minutes	X	X	X
TiC-P	30 minutes	X	X	X
Qualitative interview	60 minutes	–	–	X
Instruments administered to the therapist/case worker				
Demographics and clinical data (GAF)	Not relevant	X	–	–
AIM	Not relevant	X	X	X
SUICIDI-3.2	Not relevant	X	X	X
BAT	Not relevant	X	X	X
Receiving involuntary care	Not relevant	X	X	X

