##### AMBIT informed-MBT

2.5.1.1

The AMBIT informed-MBT condition is provided at Rivierduinen. The standard interventions offered to patients in this condition consist of MBT treatment within an AMBIT framework, including group therapy one to three times per week and one individual session weekly. If required to meet the needs of a patient, family therapy, trauma therapy (either EMDR or Narrative Exposure Therapy), mindfulness, psychodrama, pharmacotherapy, or support in areas of education, career, and housing may be included. When experience is not available within the team, emphasis is placed on seeking experience outside the team. The MBT methodology is applied/executed by trained therapists over 18 months, focusing on developing mentalizing capacity, regulating emotions, and restoring relationships. The team also received training and supervision from the Anna Freud Centre London to work according to the AMBIT methodology with the aim of building a more mentalizing network around the patient. Intervision regarding MBT and AMBIT is provided on a weekly basis.

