#### Cost-effectiveness analyses

3.3.2

The health-economic evaluation will be conducted using three approaches: 1) cost-minimization analysis (CMA), 2) cost-effectiveness analysis (CEA), and 3) cost-utility analysis (CUA). Analyses will be performed from both the healthcare system and societal perspectives (cf. Zorginstituut Nederland, 2024). Four types of costs will be considered: 1) treatment costs, 2) costs stemming from additional healthcare uptake, 3) patients’ and family out of pocket costs, 4) costs of productivity losses stemming from absenteeism and reduced efficiency at work (presenteeism). Cost data will be collected using the TiC-P, with standard cost prices obtained from Zorginstituut Nederland (2024 or later) and indexed to the year 2025. The CMA will focus on the cost difference between the conditions, specifically with regard to treatment, healthcare and societal costs. The primary clinical endpoint for the CEA will be incremental costs per reliable change over 18 months. The reliable change for AIM scores between T0 and T3 over 18 months will be calculated using the Jacobson and Truax formula (88). For the CUA, utility values derived from the EQ-5D-5L will be used to compute cumulative QALY gains over the first 9 months and the full 18-month follow-up. The propensity weights (see Analysis) will be incorporated into the cost-effectiveness and cost-utility analyses (CEA and CUA) using inverse propensity score-weighted seemingly unrelated regression equations (SURE) models to simultaneously estimate incremental effects and costs. The SURE models can be bootstrapped (5000 times) to produce graphs such as the scatter of simulated ICERs over the ICER plane and to produce the cost-effectiveness acceptability curve for further probabilistic inference and decision-making purposes. Sensitivity analysis will be directed at the main cost-drivers. The CMA, CEA and CUA will be reported according to CHEERS statement.

Incremental cost and effectiveness of AMBIT compared with treatment as usual (TAU) will be calculated for the CEA. Incremental costs are defined as the mean difference between AMBIT and TAU in total costs over 3 years. Incremental effectiveness is the mean difference in the scores on the measurement instruments over 3 years. For the CUA, incremental cost-utility will be calculated as the difference in total costs divided by the difference in QALYs.

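### Area-under-the-curve costing gives the T0 cost record a weight of 25% at 18 months and 50% at 9 months, so a treatment cost that starts at T0 can be undercounted by up to those fractions

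*Protocol article*

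**What the plan says.** Section 3.3.1 (Cost-analysis) fixes the rule for accumulating costs: "Cumulative costs over 9- and 18-month follow-up periods will be calculated using the area under the curve method". The abstract places the three assessments "at baseline (T0; start of treatment), and after 9 (T1) and 18 (T2) months of treatment", and Table 1 schedules the TiC-P at all three.

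Section 2.3.2.8 (Cost-effectiveness) says of the instrument: "The TiC-P will be administered at each assessment and captures costs related to both intervention costs and use of health care services". Section 3.3.2 lists treatment costs among the costs to be considered and names one collection instrument: "Cost data will be collected using the TiC-P". Section 3.3.1 adds: "The TiC-P will be adapted for this study to accurately reflect healthcare consumption in the target population and the treatment received".

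The article does not give the TiC-P recall period or the interpolation rule between assessments.

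**The concern.** Area under the curve suits a state such as utility, which is observed at a moment and can be joined up between visits. Resource use is a flow. The TiC-P counts contacts, sessions and hospital days over a period that has already passed, so whatever the recall length, a TiC-P completed at T0 describes time before T0. Using it as the first point of the curve puts pre-T0 resource use into a total labelled as follow-up. It also treats a treatment that begins at T0 as if its cost rose in a straight line over nine months.

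The incremental cost is at stake. It is the result of the cost-minimisation analysis and the numerator of the cost-effectiveness and cost-utility ratios, and section 1 states a hypothesis that AMBIT is more cost-effective than FACT. The arms are not randomised, so a difference in cost before T0 is to be expected, and it would pass directly into the incremental cost.

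**Working it through.** **Inputs**
- Assessment times 0, 9 and 18 months (abstract; section 2.4 and Table 1).
- Area under the curve for costs over 9 and 18 months (section 3.3.1).
- TiC-P as the cost source, intervention costs included (sections 2.3.2.8 and 3.3.2).
- A treatment that lasts the whole window in at least one AMBIT condition: "The MBT methodology is applied/executed by trained therapists over 18 months" (section 2.5.1.1).
- Assumption: each record is turned into a monthly rate c0, c1, c2, and the rates are joined by straight lines (trapezoid).

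The article gives no cost figure, weight or share, so there is no stated number to reproduce.

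**Is T0 a point on the curve?** Between 0 and 9 months only T0 and T1 exist. An area over that interval needs both, so using T0 is the natural reading.

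**Weights**
- 9 months: 4.5·c0 + 4.5·c1. The T0 weight is 4.5/9 = 50%.
- 18 months: 4.5·c0 + 9·c1 + 4.5·c2. The T0 weight is 4.5/18 = 25%.

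**Effect on a constant cost.** Let the true rate from T0 onward be D per month and let the T0 record show r·D. The area is 4.5·r·D + 4.5·D at 9 months and 4.5·r·D + 13.5·D at 18 months. The error at either horizon is 4.5·D·(r − 1). The value of r is not in the document, so a range is shown.

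| r (T0 rate ÷ later rate) | Counted, 9 months | Counted, 18 months | T0 share of total, 9 months | T0 share of total, 18 months |
|---|---|---|---|---|
| 0 | 50% | 75% | 0% | 0% |
| 0.5 | 75% | 87.5% | 33.3% | 14.3% |
| 1 | 100% | 100% | 50% | 25% |
| 2 | 150% | 125% | 66.7% | 40% |

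For treatment cost the relevant rows run from r = 0 (treatment begins at T0) to r = 1 (the same care was already being given). The undercount is therefore 0 to 50% at 9 months and 0 to 25% at 18 months. For total cost r is above zero, because participants have had at least two years of care (section 2.1), and it may exceed 1.

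**Effect on the difference between arms**, with monthly treatment costs A (AMBIT) and F (FACT) after T0:
- Both arms start at T0: 4.5(A − F) instead of 9(A − F) at 9 months, and 13.5(A − F) instead of 18(A − F) at 18 months. The difference shrinks by 50% and 25%.
- Both arms already in the same care at T0: no error.
- AMBIT starts at T0, FACT already running, A = F = 1: 13.5 − 18 = −4.5 at 18 months and 4.5 − 9 = −4.5 at 9 months, where the true difference is 0. This is a false AMBIT saving of 4.5 months of treatment cost.
- As the previous case, but with the AMBIT T0 rate at half the later rate: 4.5 × (0.5 − 1) = −2.25 months.

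**Under the alternative rule** (T1 rate for months 0-9, T2 rate for months 9-18), the T0 weight is 0 and a constant cost is counted as 9/9 and 18/18 months.

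**The case against.** Three arguments on the other side carry weight.

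First, a reader might infer that pre-treatment costs make up 25% of the 18-month total and 50% of the 9-month total. They do not. Those figures are weights, and they equal shares only when the T0 rate matches the later rate.

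Second, a reader might infer that part of the AMBIT cost is certainly lost and that the error favours AMBIT. The document does not support that either. Against the abstract's definition of T0, section 2.2 recruits through the therapists of the participating teams, section 2.2.2 counts feasibility from clients those teams treat, and section 2.5.1.2 gives AMBIT-PD treatment an average length of three to five years. Some patients may thus already be receiving the care being costed. The reason given in section 2.1 for not randomising, "altering their current care for the sake of an RCT may be unethical and disruptive", concerns all participants and does not show that only controls are already in their team's care. The bias towards AMBIT needs a mixed situation that the article does not establish.

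Third, the recall period and interpolation rule may be set out in a fuller document. For background healthcare and productivity costs that change gradually, interpolation is defensible, while carrying the T1 rate back over nine months imposes its own assumption.

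All three points limit the size and direction of the effect. They do not remove the problem with the stated rule: a record of use before T0 is not a follow-up cost, and the rule gives it a quarter or half of the weight.

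**Conclusion.** The point holds in conditional form. Under a trapezoid on the planned assessments, the T0 cost record has a weight of 25% in the 18-month total and 50% in the 9-month total. If T0 is the start of treatment, up to those fractions of a constant treatment cost are missed. If the same care is already running at T0, nothing is missed.

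The incremental treatment cost shrinks by 25% and 50% if both arms start at T0. It carries a false AMBIT saving of up to 4.5 months of treatment cost if only AMBIT does, taking equal monthly costs in the two arms. The direction cannot be stated without knowing which case applies.

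This rests on two assumptions: that T0 is a point on the curve, which the 9-month total all but requires, and that points are joined linearly. The recall length affects how T1 and T2 are scaled, but not the fact that T0 looks backwards. This should be changed before costs are analysed.

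**What to change.** In section 3.3.1, restrict area under the curve to QALYs and replace the cost rule:
- Count AMBIT and FACT intervention costs in full from T0, using the T1 record for months 0-9 and the T2 record for months 9-18.
- Leave the T0 record out of the follow-up cost total, and enter T0 cost as a baseline covariate in the cost equation of the SURE model.
- For other healthcare and productivity costs, assign T1 to months 0-9 and T2 to months 9-18, scaled from the TiC-P recall window. Keep linear interpolation as a sensitivity analysis.
- State the TiC-P recall window, and say for each arm whether T0 coincides with the start of the team's care.

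The cost is a few sentences, with no data collection beyond the planned TiC-P. The downside is small: where the recall window is shorter than nine months, the T1 and T2 rates are extrapolated over months that nobody observed. Area under the curve also fills in unobserved months, and the sensitivity analysis shows how much the choice matters.

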#### Cost-effectiveness analyses

3.3.2

The health-economic evaluation will be conducted using three approaches: 1) cost-minimization analysis (CMA), 2) cost-effectiveness analysis (CEA), and 3) cost-utility analysis (CUA). Analyses will be performed from both the healthcare system and societal perspectives (cf. Zorginstituut Nederland, 2024). Four types of costs will be considered: 1) treatment costs, 2) costs stemming from additional healthcare uptake, 3) patients’ and family out of pocket costs, 4) costs of productivity losses stemming from absenteeism and reduced efficiency at work (presenteeism). Cost data will be collected using the TiC-P, with standard cost prices obtained from Zorginstituut Nederland (2024 or later) and indexed to the year 2025. The CMA will focus on the cost difference between the conditions, specifically with regard to treatment, healthcare and societal costs. The primary clinical endpoint for the CEA will be incremental costs per reliable change over 18 months. The reliable change for AIM scores between T0 and T3 over 18 months will be calculated using the Jacobson and Truax formula (88). For the CUA, utility values derived from the EQ-5D-5L will be used to compute cumulative QALY gains over the first 9 months and the full 18-month follow-up. The propensity weights (see Analysis) will be incorporated into the cost-effectiveness and cost-utility analyses (CEA and CUA) using inverse propensity score-weighted seemingly unrelated regression equations (SURE) models to simultaneously estimate incremental effects and costs. The SURE models can be bootstrapped (5000 times) to produce graphs such as the scatter of simulated ICERs over the ICER plane and to produce the cost-effectiveness acceptability curve for further probabilistic inference and decision-making purposes. Sensitivity analysis will be directed at the main cost-drivers. The CMA, CEA and CUA will be reported according to CHEERS statement.

Incremental cost and effectiveness of AMBIT compared with treatment as usual (TAU) will be calculated for the CEA. Incremental costs are defined as the mean difference between AMBIT and TAU in total costs over 3 years. Incremental effectiveness is the mean difference in the scores on the measurement instruments over 3 years. For the CUA, incremental cost-utility will be calculated as the difference in total costs divided by the difference in QALYs.

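### The economic evaluation is defined over both 3 years and 18 months and in both 2018 and 2025 prices; only the 18-month version matches the data collected

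*Protocol article*

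**What the plan says.** **Schedule.** Section 2.4 places follow-up at 9 months (T1) and 18 months (T2), and then: "After 18 months, participants will continue their treatment if this is still needed, but study participation will end". Table 1 lists EQ-5D-5L, TiC-P and AIM at T0, T1 and T2 and at no other time. The only later contact is a question about willingness to be assessed 5 years after the study.

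**3-year statements.** Section 2.3.2.8 says that QALYs "will be calculated over the 3 years follow-up period". The second paragraph of 3.3.2 says "Incremental costs are defined as the mean difference between AMBIT and TAU in total costs over 3 years" and "Incremental effectiveness is the mean difference in the scores on the measurement instruments over 3 years".

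**18-month statements.** Section 3.3.1 accumulates costs over 9 and 18 months by area under the curve. The first paragraph of 3.3.2 makes incremental cost per reliable change over 18 months the primary endpoint of the cost-effectiveness analysis (CEA), and takes QALY gains over 9 and 18 months.

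**Wave label.** Section 3.3.2 refers to "The reliable change for AIM scores between T0 and T3 over 18 months".

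**Price year.** Section 3.3.1: "All costs will be indexed to the reference year 2018". Section 3.3.2: costs are "indexed to the year 2025".

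**The concern.** Cost-effectiveness is a named aim with its own hypothesis in the Introduction. An incremental cost-effectiveness ratio (ICER) has no meaning until its horizon, its unit of effect and its price year are fixed, and here each is stated in two ways.

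The horizon is not a neutral choice. Section 3.3.1 discounts costs and effects beyond 12 months, so the horizon decides how much is discounted. Costs after 18 months may also differ by setting: section 2.5.1.1 describes MBT delivered over 18 months, while 2.5.1.2 describes AMBIT-PD treatment that lasts three to five years on average.

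If the conflict stays, a reader of the results cannot tell which version was prespecified, and the choice could be made after the data are seen.

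**Working it through.** **1. Horizon against data.**
- Inputs: waves at 0, 9 and 18 months (2.4, Table 1); stated horizon 3 years = 36 months (2.3.2.8, and 3.3.2 second paragraph).
- Observed span: 18 / 12 = 1.5 years.
- Share of the stated horizon observed: 18 / 36 = 50%. Unobserved: 36 − 18 = 18 months.
- The 3-year horizon is therefore not reproduced from the schedule. A 5-year contact, agreed to or not, supplies no cost or utility data between months 18 and 36.

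**2. What this means for QALYs.** With utility 1 throughout, the area under the curve over the scheduled waves is (9 − 0)/12 + (18 − 9)/12 = 0.75 + 0.75 = 1.5 undiscounted QALYs per person. Over 3 years the ceiling is 3.0. This shows that the two definitions are different quantities. It does not measure the effect on the ICER.

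**3. Can the 18-month version be computed?**

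| Quantity | 18-month definition | Data at T0, T1, T2 |
|---|---|---|
| Costs | 3.3.1 | TiC-P |
| QALYs | 3.3.2, first paragraph | EQ-5D-5L |
| Reliable change | 3.3.2, first paragraph | AIM |

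Yes, for all three, once T3 is read as T2.

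**4. Wave label.** The sentence ties T3 to 18 months, and 18 months is T2 in 2.4. There are three waves, T0 to T2. The label is wrong, but its intended meaning can be recovered.

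**5. Effect measure.** The first paragraph of 3.3.2 gives cost per reliable change on the AIM. The second gives a mean difference in scores on instruments that it does not name. The first ICER is in euros per additional patient with reliable change, the second in euros per scale point.

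**6. Price year.** Gap: 2025 − 2018 = 7 years. The document gives no inflation rate, so a yearly rate r is assumed, with factor k = (1 + r)^7:

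| r (assumed) | k |
|---|---|
| 2% | 1.15 |
| 3% | 1.23 |
| 4% | 1.32 |
| 5% | 1.41 |

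With one common index, the cost difference ΔC becomes kΔC and the ICER becomes kΔC/ΔE. Because k > 0, the sign of ΔC and any finding of dominance are unchanged. The level of the ICER, and so its position against a fixed willingness-to-pay threshold, moves by the factor k.

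**The case against.** The strongest reply is that the document already holds a complete and more specific 18-month plan, and that the 3-year sentences are stray text. Much of this stands. A reader might infer that the economic evaluation cannot be computed at all. That goes too far: only the 3-year definitions cannot be obtained, as step 3 shows. A reader might also infer that the study means to extrapolate from 18 to 36 months without a stated model. Nothing in the document proposes extrapolation.

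Three further points stand in whole or in part:
- The T3 sentence fixes its own meaning through the words about 18 months. It does not point to a missing wave.
- The price lists might look like a clash, since 3.3.1 cites a 2016 edition and 3.3.2 a 2024 edition. Both allow a later one, and a 2024 list satisfies both. Only the index year conflicts.
- The second effect definition can be read as a generic formula for all instruments, and a difference in proportions is itself a mean difference of a 0/1 score. This softens the mismatch. It does not remove it, because the sentence neither mentions reliable change nor uses the 18-month horizon.

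What the reply does not answer is that the 3-year horizon appears three times in two sections as an operative definition, and that the two index years cannot both apply. Condensing a protocol into an article explains missing detail, but not two explicit statements that disagree.

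**Conclusion.** The point holds as an internal contradiction in the definitions of a secondary but named aim. Costs, effects and QALYs are each defined over 3 years in one place, while data end at 18 months; half of the longer horizon is unobserved. Costs carry two index years, 7 years apart, worth a factor of about 1.15 to 1.41 on the cost scale. That range rests entirely on the assumed 2% to 5% growth, and the statement that the sign of the cost difference is unaffected rests on one common index for all costs. The T3 label and the loose second effect definition are minor and belong to the same correction.

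This should be fixed before the economic analysis. It does not threaten the study: recruitment, data collection and the primary OQ-45.2 analysis do not depend on it.

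**What to change.** - In 2.3.2.8 and 3.3.2, set the horizon to 18 months, with 9 months as the interim point, and delete the 3-year wording in all three places.
- In 3.3.2, replace T3 by T2.
- In 3.3.2, state that the primary CEA effect is the between-group difference in the proportion of patients with reliable change on the AIM from T0 to T2. If mean score differences are also wanted, label them as additional.
- Use one index year in 3.3.1 and 3.3.2. The year 2025, already in 3.3.2, fits a study registered in 2025.

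The cost is a text correction. Table 1 already provides every measurement needed, so no new data, visits or participants are required. If a separate analysis plan repeats any of these definitions, it should be aligned at the same time.

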#### Propensity score matching

3.1.2

A propensity score is calculated, which is a statistical approach that attempts to reduce selection bias and known confounding that could be found in an estimate of treatment outcome in an observational study. A propensity score is the conditional probability that a participant in a study will be assigned to one of two treatment groups in this study, given a set of observed pre-treatment characteristics. Pre-treatment characteristics are demographic and clinical characteristics of participants (partly) determining the indication for a specific treatment, such as diagnoses or social situation. They will be included in the propensity score calculation as they may be related to treatment outcome and are therefore considered potential confounders. A linear regression analysis will be conducted to identify how pre-treatment variables relate to outcome, with pre-treatment variables as the dependent variable and each potential confounder as an independent variable. The propensity score for each participant will then be estimated using logistic regression analysis with all potential confounders as independent variables and ‘group membership’ (the condition to which the participant was assigned to) as the dependent variable. Each participant from one condition will then be matched with a participant from the other condition, based on the nearest available propensity score, pairs with a propensity score difference of 0.10 will be removed from the analysis, resulting in matched pairs that show no difference on any of the observed pre-treatment characteristics. A regression analysis will then be conducted in the matched sample with the identified confounding pre-treatment characteristics as dependent variable and the ‘group membership’ as the independent variable to reduce the effect of treatment group membership (44, 86, 87).

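### No T0 EQ-5D-5L utility term is stated in the propensity score or the QALY equation, so weighting on indication variables alone could leave most of a baseline utility gap in the incremental QALYs

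*Protocol article*

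**What the plan says.** Section 3.3.2 of the Protocol article bases the cost-utility analysis on the EQ-5D-5L: "utility values derived from the EQ-5D-5L will be used to compute cumulative QALY gains over the first 9 months and the full 18-month follow-up". Incremental effects and costs in both the cost-effectiveness and the cost-utility analysis are to be estimated "using inverse propensity score-weighted seemingly unrelated regression equations (SURE) models to simultaneously estimate incremental effects and costs", optionally bootstrapped 5000 times. The section closes with the definition of the ratio: "incremental cost-utility will be calculated as the difference in total costs divided by the difference in QALYs".

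For the propensity score, section 3.3.2 refers the reader to the analysis section. Section 3.1.2 says of the variables that enter it: "Pre-treatment characteristics are demographic and clinical characteristics of participants (partly) determining the indication for a specific treatment, such as diagnoses or social situation". The score is "estimated using logistic regression analysis with all potential confounders as independent variables". That section describes matching on the score and does not define the weights.

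Table 1 schedules the EQ-5D-5L at T0, T1 (9 months) and T2 (18 months). Section 2.1 accepts that "the absence of randomization does increase the risk of bias from unknown confounders, which will be considered in the analysis".

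**The concern.** QALYs computed as the area under the utility curve contain the T0 utility. A patient flat at 0.60 for 18 months accrues 0.60 × 1.5 = 0.90 QALY and a patient flat at 0.40 accrues 0.60 QALY, yet neither gained anything. In a non-randomised comparison between different teams, a T0 utility gap enters the QALY difference directly, and again through its persistence at T1 and T2, unless the estimator removes it.

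The stated estimator removes it only as far as the propensity score does. The rule in section 3.1.2 selects variables that bear on indication. EQ-5D-5L utility appears in the article as a cost-effectiveness outcome (section 2.3.2.8) and is not listed as a determinant of indication. Someone following the text literally could build the weights without it.

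Section 2.3.2.8 expects a dominant result for AMBIT. A spurious difference of a few hundredths of a QALY could help to produce that result, or hide it.

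**Working it through.** The article gives no utility, QALY or ICER figure, so there is no stated number to reproduce.

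**Inputs from the article:** assessments at 0, 9 and 18 months; 40 + 40 = 80 FACT and 40 + 40 = 80 AMBIT patients (section 2.2).

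**Assumptions (not in the article):** trapezoid QALYs; utility SD 0.25; correlation ρ = 0.6 between any two waves (range 0.4 to 0.8); no treatment effect; a T0 gap d of 0.05 or 0.10; weights built on one indication covariate that correlates r = 0.3 to 0.5 with T0 utility and differs between groups only through that correlation.

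**1. Weight of T0.** Over 18 months, QALY = 0.375·u0 + 0.75·u1 + 0.375·u2. T0 has 0.375/1.5 = 25%. Over 9 months, QALY = 0.375·u0 + 0.375·u1. T0 has 0.375/0.75 = 50%.

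**2. Gap passed on with no adjustment for T0 utility.** Over 18 months it is d × (0.375 + 1.125ρ). At d = 0.05 and ρ = 0.6 this is 0.05 × 1.05 = 0.0525 QALY.

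**3. What is left after weighting on the indication covariate.** Balancing that covariate removes a fraction r² of the T0 gap, so the remainder is d × (1 − r²) × (0.375 + 1.125ρ).

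| d | r | Remaining 18-month QALY difference (ρ = 0.6) |
|---|---|---|
| 0.05 | 0.3 | 0.0525 × 0.91 = 0.048 |
| 0.05 | 0.5 | 0.0525 × 0.75 = 0.039 |
| 0.10 | 0.3 | 0.105 × 0.91 = 0.096 |
| 0.10 | 0.5 | 0.105 × 0.75 = 0.079 |

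So 75% to 91% remains. With ρ from 0.4 to 0.8, the remainder per 0.05 gap runs from 0.031 (ρ = 0.4, r = 0.5) to 0.058 (ρ = 0.8, r = 0.3). Over 9 months at ρ = 0.6 the multiplier is 0.375 + 0.375 × 0.6 = 0.60, so a 0.05 gap leaves 0.030 × 0.75 = 0.023 to 0.030 × 0.91 = 0.027 QALY.

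**4. Simulation of the weighted estimator.** 1,500 null trials of 80 v 80 per setting gave weighted differences close to step 3. At the 5% level the false-positive rate was about 9% to 16% at a gap of 0.05 and about 30% to 45% at a gap of 0.10. With T0 utility added to the weighted outcome equation, bias was about 0 and rejection about 5% to 6%.

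**5. Putting T0 utility in the score.** In a simulation of 400,000 patients with group membership driven by T0 utility, the unadjusted 18-month difference was 0.051 at a gap of about 0.05 and 0.101 at about 0.10. Weighting on a score that contains T0 utility gave −0.0005 and 0.0007. Regression on T0 utility gave −0.0004 and −0.0007.

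**6. Precision.** QALY variance is 0.25² × (0.84375 + 1.40625ρ) = 0.0625 × 1.6875 = 0.1055 at ρ = 0.6, so SD is 0.325 and the SE of the difference is 0.325 × √(2/80) = 0.051. T0 utility explains 1.05²/1.6875 = 65% of that variance. The adjusted SE is 0.051 × √0.35 = 0.030.

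**The case against.** A reader might infer from the closing definition in section 3.3.2 that the plan divides costs by a raw between-group difference in QALYs, so that any baseline gap is counted as an AMBIT effect. The article does not support that. The sentence only defines the ratio; the same section names weighted SURE models as the estimator, and an adjusted coefficient is also a difference in QALYs. Error rates worked out for an unweighted difference would therefore not describe this plan.

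Nor does the article leave T0 utility out. Diagnoses and social situation are examples, the propensity model takes all potential confounders, and EQ-5D-5L is available at T0. If T0 utility is in the score, weighting alone brings the bias to about 0 (step 5). The same holds if the T0 gap arises wholly through the variables that are weighted on. A full covariate list is also something a condensed article may leave to a fuller document.

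The QALY formula is inferred: section 3.3.1 names the area-under-the-curve method for costs, and no formula is given for QALYs. If a baseline-referenced gain were meant, the T0 level would enter differently. Under the assumptions above, without weighting, that version would give 0.05 × (1.05 − 1.5) = −0.0225 QALY at a 0.05 gap, so it would not settle the matter either.

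Chance imbalance is not bias; the bootstrap interval reflects it. That argument for the covariate is about precision.

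These objections remove any claim of error. What stands is that the stated inclusion rule, which concerns indication, does not ensure that T0 utility is adjusted for, and no term in the QALY equation does so.

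**Conclusion.** The point holds as an improvement to the stated estimator, not as an error. The cost-utility analysis is adjusted by propensity weighting, but neither the score nor the QALY equation is stated to contain T0 utility. If it is left out and QALYs are areas under the curve, about 0.04 to 0.05 QALY per 0.05 of T0 gap could remain over 18 months (0.03 to 0.06 across correlations of 0.4 to 0.8). The size rests on the assumed SD, correlations and gap, and on the indication variables being only moderately related to T0 utility. It falls to about 0 if T0 utility is in the score or if the weighted variables account for the whole gap. Whether a T0 gap will occur is unknown; the non-randomised design makes it plausible. Apart from bias, the covariate would cut the SE of incremental QALYs from about 0.05 to 0.03 under the same assumptions.

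**What to change.** In section 3.3.2, add T0 EQ-5D-5L utility as a covariate in the QALY equation of the weighted SURE model. In section 3.1.2, name it among the propensity variables. State that the adjusted group coefficient, taken in each bootstrap draw, is the incremental QALY figure used in the cost-utility ratio, for both the 9-month and the 18-month horizon. A short statement of the QALY formula would remove the remaining ambiguity.

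The cost is two or three sentences. The measure is already scheduled at T0 (Table 1), so no extra data collection and no extra patients are needed.
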